### Intervention

2.7

#### Control group: usual care

2.7.1

Both groups of participants will continue to receive “usual care” during the 10-week intervention. Usual care refers to any therapeutic treatment or service that the child would normally receive outside of the intervention study. The researcher will evaluate children's condition, we expected that most participants in this study will not access additional therapy as possible.

#### Treatment group: hydrotherapy and tDCS

2.7.2

Our intervention plan is based on Akinola et al's^[17]^ research on hydrotherapy and studies about tDCS.^[30,44,45]^

The participants in the treatment group will receive a treatment protocol which is about specific plans and measures during treatment. Participants will receive exercise training in water, 2 times a week for 10 weeks, with the exercise area fully immersed in water. The water temperature will be controlled between 28°C and 31°C throughout the whole duration of intervention. Two physical therapists will be involved in the treatment of each participants in a treatment session. The exercise program contains 2 categories of exercises as follows.

Exercise 1 (manual passive stretching). This will include passively moving the joint involved in the spastic muscle group away from the direction of the main function and maintain this position for 60 seconds, where the muscle group is fully extended. This process will be repeated 5 times for each part, with a total duration of 5 minutes.

Exercise 2 (functional training). All children will receive 4 levels of functional training according to their dysfunction levels, and each level of training lasted 15 minutes. The 4 levels are the following:

Level 1: 2-point kneeling exercise trainingLevel 2: Sitting education/trainingLevel 3: Standing education/trainingLevel 4: Walking education/training

Two neurologists with ample experience in noninvasive cerebral stimulation will oversee the evaluations for the indication of tDCS. tDCS will be performed during the intervention sessions, it is reported that tDCS can promote behavioral changes through building a neural network that is conducive to the environment. Our study will employee the tDCS Transcranial Stimulation equipment producted by Soterix Medical Inc. The device works by 2 5 × 5 cm^2^ nonmetallic sponge surface electrodes immersed in saline solution. The anodal electrode will be in the dominant brain hemisphere area over C3, following the internationally standardized 10 to 20 electroencephalogram system, corresponding to the primary motor cortex, and the cathode will be located in the contralateral supraorbital area.^[45]^ No stimulation will be provided throughout the rest of the session, which is a valid control procedure in studies involving tDCS. The current will be applied to the primary motor cortex for 20 minutes in the middle of each training session. The device has a button and the operator can control the intensity of the current. The stimulation will increase from 0 to 1 mA and gradually reduced in the final 10 seconds. The tDCS will be repeated once a day, 3 times a week, a total of 30 treatments

We initially plan to carry out tDCS on Mondays, Wednesdays, and Fridays, and hydrotherapy on Thursdays and Sundays.

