## Introduction

1

Cerebral palsy (CP) is a neurodevelopmental disorder caused by a brain injury resulting in poor coordination and motor control deficits, which is one of the most widespread physical deformity in children.^[1]^ This disorder commonly occurs in 2.11 cases per 1000 live births and are widely recognized for causing dystonia, motor, and movement dysfunction, and intellectual disability.^[2,3]^ A previous meta-analysis demonstrated that the prevalence of CP among children aged 0 to 6 years in China is 0.23%.^[4]^ The European surveillance of CP group described the motor type of CP as spastic, dyskinetic (dystonia, chorea, and athetosis), ataxic and mixed types involving the mentioned types.^[5]^ Spastic cerebral palsy is the most common type of this movement disorder, which occurs in more than 80% in children.^[6]^ CP is usually diagnosed in childhood, but its course can last into adolescence, adulthood, and has different severity. There are evidences that children with CP have a higher rate of deterioration of physical and mental function and a higher risk for secondary diseases.^[3,7]^ It is reported that the cost of care for each child is estimated at $921,000 in the US.^[8]^ CP brings a heavy burden on families and society and becomes a significant public health issue.^[9]^

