The conventional treatment for children with CP is made up of medical treatment, physical therapy (PT), occupational therapy, psychotherapy, surgical therapy, virtual reality technology, hyperbaric oxygen therapy, stem cell transplantation, and speech therapy.^[10–12]^ Almost all these treatments are aimed at improving patient activity and functional participation, however, none of them can completely cure CP. In recent years, PT as a treatment for CP is developing rapidly, which is a special treatment method based on physical factors such as sound, electricity, light, force, water, magnetism, and thermal power. Owing to the risks of neurosurgery and side effects of pharmacological intervention, PT becomes the central part of rehabilitation for children with CP.^[13,14]^ Among them, hydrotherapy promotes children's voluntary and passive movement in the water through the resistance, buoyancy, static pressure, and warming effects of water, which is beneficial to improve human blood circulation and relax the muscles of the whole body, thereby promoting the alleviation of muscle spasm and the reduction of muscle tension, and then improves the children's balance ability, expands the joint range of motion.^[15]^ Numerous studies have pointed out that the potential of hydrotherapy programs have significant benefits for children with CP.^[15,16]^ The result of a 10-week aquatic exercise training program is effective in the functional rehabilitation of children with spastic CP.^[17]^ A previous systematic review published in 2017 suggested that evidence on aquatic interventions for children with CP is limited since only 2 used randomized control trial design, and the results were mixed.^[18]^ Another systematic review published in 2021 showed that hydrotherapy can help improve the motor function and activities of children and adolescents with CP, and may improve their quality of life, which included 9 randomized controlled trials (RCTs).^[19]^

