### Participants

2.2

Participants meeting the following inclusion criteria will be included: CP patients between 4 and 14 years old, CP was diagnosed according to the Subspecialty Group of Rehabilitation of Chinese Medical Association,^[32]^ voluntary participation and informed consent signed. Participants with any of the following exclusion criteria will be excluded: visual, auditory, and mental disorders affecting the results assessment; children with epilepsy who are uncontrolled with medication; skin problems such as open wounds or active infection; receiving botulinum toxin injections or surgery no earlier than 6 months before project start; participation in another clinical trial; unconscious, behaving strangely or uncontrollably, and are prone to medical accidents during treatment.

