### Outcome measures

2.6

We will evaluate the CP children using questionnaires at the beginning of the treatment, within 1 week after 10 weeks of therapy, 4 weeks, and 12 weeks after the last intervention. Descriptive measures and characteristics, such as age, gender, body weight, type of CP and the outcomes were recorded for all study participants. All patient related data will be safely collected and stored. Only researchers related to the study will be allowed to access to the trial dataset. The primary outcomes of this study are Gross Motor Function Assessment and Pediatric Balance Scale (PBS) between the treatment group and the control group. The secondary outcomes are the difference in Pediatric Evaluation Disability Inventory (PEDI), adverse effects between the control and treatment groups.

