## Discussion

3

According to incomplete statistics, there were about 5.3 million patients with CP in China in 2018, and it is increasing at a rate of about 50,000 per year. The investigation report of children with CP in 12 provinces in China pointed out that the incidence of CP in children aged 1 to 6 years was 2.48‰, and the most common type of CP was spastic CP, which accounted for 58.86% of children with CP. Children with spastic CP are unable to stand, sit up and walk normally due to rigid extension reflexes, overexcited reflexes, and abnormal muscle stiffness, which is the main cause of severe motor disability in children.^[46]^ Children with CP are a huge group, and their treatment and rehabilitation is an important task in our country. Rehabilitation therapy plays a key role in the management of CP in children. It can help children with CP to maximize their potential for physical independence and health, and minimize the impact of physical injury. At present, the rehabilitation treatment of CP is mainly based on PT, including exercise therapy, hydrotherapy, occupational therapy, and tDCS. Among the outcome indicators such as motor function and balance function, it has been proven that hydrotherapy and tDCS are effective for children with CP. This study protocol describes a RCT study design which will test the comparative effectiveness of combining hydrotherapy and tDCS. The outcome evaluations will include analyses of GMFM-88, PBS. If the combination of hydrotherapy and tDCS is proven to be superior to the other in some of these aspects, this evidence would permit professionals to recommend the ideal PT for patients with CP, which will minimize their incapacity and optimize their rehabilitation. It is hoped that findings from this research will be published and disseminated in an internationally recognized, peer-reviewed journal.

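### Eligibility is open to every type of CP, but Exercise 1 of the water programme is defined only for spastic muscle, and nothing says what other eligible children receive

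*Protocol article*

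**What the plan says.** Section 2.2 (Participants) defines the population once: "CP patients between 4 and 14 years old, CP was diagnosed according to the Subspecialty Group of Rehabilitation of Chinese Medical Association". Neither the inclusion nor the exclusion criteria mention motor type. The Introduction lists the types as "spastic, dyskinetic (dystonia, chorea, and athetosis), ataxic and mixed types involving the mentioned types".

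Section 2.7.2 splits the water programme into two exercise categories. Exercise 1, passive stretching, is described as follows: "This will include passively moving the joint involved in the spastic muscle group away from the direction of the main function". Exercise 2 is functional training by level of dysfunction and is given to every child. tDCS is given 30 times and is not tied to CP type. The section bases its hydrotherapy on an earlier study, which the Introduction summarises thus: "The result of a 10-week aquatic exercise training program is effective in the functional rehabilitation of children with spastic CP".

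Two background figures for the spastic share appear. The Introduction says: "Spastic cerebral palsy is the most common type of this movement disorder, which occurs in more than 80% in children". The Discussion reports a survey of children aged 1 to 6 in 12 Chinese provinces, in which "the most common type of CP was spastic CP, which accounted for 58.86% of children with CP".

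Type of CP is collected (section 2.6): "Descriptive measures and characteristics, such as age, gender, body weight, type of CP and the outcomes were recorded for all study participants". It is not mentioned in the description of the envelopes (section 2.4) or of the between-arm comparison (section 2.8).

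**The concern.** A child with purely dyskinetic or ataxic CP meets section 2.2 but has no muscle group to which Exercise 1, as worded, applies. The therapist must then omit the stretch, replace it or reinterpret it, and the article gives no rule. What the treatment arm receives would then vary with CP type in an undocumented way.

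Two statistical consequences could follow. If these children gain less, the single GMFM-88 or PBS comparison averages over different responses, and a null result is harder to interpret. CP type may also be related to the motor scores themselves: the Discussion links spastic CP to severe motor disability. If type plays no part in allocation or analysis, a chance imbalance between the arms adds noise that a variable already collected could remove.

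**Working it through.** **The plan's own figure.** Section 2.3 gives 150 children (75 per arm) but no effect size, SD or power, so the total cannot be reproduced and there is no planning effect to compare with. The power figures below are illustrations only.

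**How many children could be affected**
- Introduction: spastic share above 80%, so other types are below 1 − 0.80 = 20%. 75 × 0.20 = 15 treated children, 30 of 150. Because the source says more than 80%, this is a ceiling for that source.
- Discussion: 1 − 0.5886 = 41.14%. 75 × 0.4114 = 30.9, about 31 treated children; 150 × 0.4114 = 61.7, about 62 in all.
- Both complements include mixed types, some of which involve spasticity, so both overstate the number with no spastic muscle.

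**How much of the treatment is affected**
- Exercise 1: 5 minutes as stated × 2 sessions a week × 10 weeks = 100 minutes. The 5 minutes equals 5 holds of 60 seconds for one body part; if several parts are stretched, the time is longer.
- Water time with one 15-minute level of Exercise 2: 20 × (5 + 15) = 400 minutes, so Exercise 1 is 100/400 = 25%. With all four levels: 20 × (5 + 60) = 1,300 minutes, so 100/1,300 = 7.7%.
- Adding tDCS (30 × 20 = 600 minutes): 100/1,000 = 10%, or 100/1,900 = 5.3%.

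**What dilution would do, under assumptions**
- SE of a standardised mean difference with 75 per arm: √(2/75) = 0.163.
- Assumed effect in spastic children: the one detected with 80% power at two-sided 0.05 (sidedness is not stated), (1.960 + 0.842) × 0.163 = 0.457 SD.
- With p the non-spastic share and L the assumed fraction of effect they lose, the pooled effect is 0.457 × (1 − pL). Power = Φ(pooled effect/0.163 − 1.96).

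| Assumed loss L | p = 20%: factor, power | p = 41.14%: factor, power |
|---|---|---|
| 0 | 1.00, 80% | 1.00, 80% |
| 10% | 0.98, 78% | 0.959, 77% |
| 50% | 0.90, 71% | 0.794, 60% |

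The documents give no value for L.

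**Chance imbalance if allocation ignores type.** The 95% range for the difference between arms in non-spastic share is ±1.96 × √(2p(1 − p)/75): ±12.8 percentage points at p = 20% and ±15.8 at p = 41.14%.

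**The case against.** Several stronger readings are tempting, and the documents do not support them.

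- A reader might infer that the population is defined in two conflicting ways. It is defined once, in section 2.2. Exercise 1 describes a treatment component, and the earlier spastic-CP programme sets no eligibility here.
- A reader might infer that 20–41% of treated children cannot receive the intervention. Only the stretch is undefined for them; Exercise 2 and tDCS are not restricted by type. The percentages are background prevalences that count mixed types, and the larger comes from ages 1 to 6, whereas the trial enrols ages 4 to 14.
- A reader might take dilution as established. No effect by type is given. The extreme case, in which non-spastic children gain nothing (factors 0.80 and 0.589, power 61% and 38%), would require the missing stretch to cancel all benefit of the functional training and 30 tDCS sessions. No passage supports that.
- A reader might infer that allocation is unstratified. Section 2.4 describes concealment and is silent on stratification, which a condensed article may leave out. Chance imbalance is in any case not bias under randomisation.
- A pooled intention-to-treat effect over all enrolled types is the effect for the population in section 2.2, so a conclusion about patients with CP is consistent with the design. Limiting it to children who received the full programme would leave the randomised comparison.

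It can also be said that section 2.7.2 refers to a treatment protocol, where the missing rule may sit. That tempers the point without removing it: the article states both the eligibility and the exercise, and the two do not fit together as printed.

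**Conclusion.** The mismatch stands: some children eligible under section 2.2 have no defined Exercise 1 under section 2.7.2. The number affected is bounded at about 15 to 31 of 75 treated, on the article's background shares and with every mixed-type child counted as non-spastic. The part of the treatment affected is small as stated, 100 minutes over 20 water sessions.

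The pooled effect may be diluted, by an amount the documents do not determine. The loss could be negligible or, if non-spastic children were assumed to lose half the effect, could take power from 80% to 60–71%. Those powers rest wholly on the assumed 0.457 SD and the assumed loss. The point is worth correcting because the change is cheap; it does not invalidate the randomised comparison.

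**What to change.** Reconcile sections 2.2 and 2.7.2, so that either the eligible children and those for whom Exercise 1 is defined coincide, or the text states what the treatment arm receives when there is no spastic muscle group. That choice is clinical and belongs to the sponsor.

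If all types stay eligible:
1. Stratify the sealed envelopes by CP type: spastic or mixed with spasticity, against other. If this is already done, say so in section 2.4.
2. Include CP type as a factor in the between-arm analysis of GMFM-88 and PBS in section 2.8. If the rank-based route is taken, use a stratified rank test, because the Kruskal-Wallis test cannot carry a second factor.
3. Treat any effect by type as supportive only, and keep the main conclusion with the whole randomised population.

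The cost is a second envelope series, slightly more allocation administration and one extra model factor. CP type is already recorded, though the strata require noting whether a mixed type includes spasticity.

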### Statistical analysis

2.8

An experienced statistician will conduct the data analysis. When necessary, intention to treat analysis will be used with the data from the previous evaluation repeated to substitute missing data. We will use the Kolmogorov-Smirnov test to demonstrate normal data distribution. Thus, Parametric data will be presented as mean (standard deviation) as well as nonparametric data will be presented as median (inter-quartile interval). The effect size will be calculated by the difference between means of the pre-intervention and post-intervention evaluations and will be presented with the respective 95% confidence interval. The independent *t* test and chi-square tests will be applied to assess and compare the baseline patient characteristics between the treatment and the control groups. Either 2-way ANOVA or the Kruskal-Wallis test will be used for the statistical analysis of the effects of control group or treatment group for parametric and nonparametric variables, respectively. The Bonferroni correction for multiple comparisons will be employed as the post hoc test. Statistical significance will be considered at a *P* value of <.05. The data will be organized and tabulated using the Statistical Package for the Social Sciences (SPSS) version 19.0 (IBM, Armonk, NY, USA).

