To sum up, when hydrotherapy and tDCS are used to treat separately, it has positive therapeutic effect in children with CP. The development of new therapies in combination with physical rehabilitation approaches is critical to optimize functional outcomes. tDCS has attracted interest in this context, as significant functional improvements have been demonstrated in individuals with brain injuries after a short period of cerebral stimulation. Since the onset of this work, tDCS has been used in combination with constraint-induced therapy, gait and mobility training, virtual reality therapy to potentiate the treatment effect.^[29–31]^ Up to now, there are no studies on the effect of a combined application of hydrotherapy and tDCS in children with CP. We will conduct a 2-arm parallel clinical trial to investigate the effect of a combined application of tDCS and hydrotherapy. We hypothesized that tDCS combined concurrently with hydrotherapy would result in the greater and longer-lasting improvement in motor function.

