### Study design

2.1

This study is an outcome assessor and data analyst-blinded, randomized, controlled superiority trial and will be conducted at the Second Affiliated Hospital of Qiqihar Medical University, from October 2021 to December 2023. CP patients who meet the inclusion criteria will be allocated in a 1:1 ratio into the treatment group (hydrotherapy plus tDCS, n = 75, expected), or the control group (treatment as usual, n = 75, expected). All participants will receive 30 sessions of treatment over 10 weeks. The study design is presented in Figure 1.

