### Sample size

2.3

The necessary sample size has been estimated based on study of Whitehead et al,^[33]^ which estimated the minimum sample size of a pilot randomized trial with a continuous outcome variable. A previous RCT protocol about the effect of bilateral anodal tDCS vs treadmill training on brain activities of children with CP also used this Sample size estimation method. In our study, the Gross Motor Function Measure (GMFM) score which is a continuous outcome variable, is regarded as a primary outcome. The result is that 150 children with CP will undergo intervention or control group and will be assessed just once during pretest assessment to consider their results as a reference value for later comparisons. However, there is a lack of official pediatric reference values in GMFM of study on the combination of hydrotherapy and tDCS. Compared with the results of a meta-analysis, the sample size of our study is larger than that of each RCT on tDCS.^[34]^ Therefore, generalization of reference values from this study should be made with caution.

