### Evaluation and follow-up

2.5

Two experienced physical therapists who blind to which group each child belongs will evaluate the both group in the evaluation procedures. Four evaluations will be conducted:

First evaluation: 1 week before intervention;Second evaluation: 1 week after the last intervention;Third evaluation: 4 weeks after the last intervention;Fourth assessment: 12 weeks after the last intervention.These evaluations will be conducted on 2 nonconsecutive days.

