## Conclusion

4

In conclusion, this protocol describes an outcome assessor and data analyst-blinded, randomized, controlled superiority trial that aims to investigate the efficacy of a combined application of tDCS and hydrotherapy in patients with CP. The results will ascertain whether tDCS combined concurrently with hydrotherapy would result in the greater and longer-lasting improvement in motor function. The findings will be of great significance for clinical practice about treating CP.

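### Filling missing scores with the previous evaluation builds an assumption about persistence into the 4- and 12-week results that are meant to test persistence

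*Protocol article*

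**What the plan says.** Section 2.8 (Statistical analysis) states: "When necessary, intention to treat analysis will be used with the data from the previous evaluation repeated to substitute missing data". This is last observation carried forward, and the article names no other way of handling missing scores. The comparison of groups is then by 2-way ANOVA or, for non-parametric variables, the Kruskal-Wallis test.

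Section 2.5 (Evaluation and follow-up) sets one evaluation before treatment and three after it. The first of the three is described as "Second evaluation: 1 week after the last intervention", the next comes at 4 weeks, and the last is described as "Fourth assessment: 12 weeks after the last intervention". No evaluation is planned during the 10-week course.

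The Introduction hypothesises that the combination "would result in the greater and longer-lasting improvement in motor function". Section 4 (Conclusion) repeats this as what the trial will settle: "The results will ascertain whether tDCS combined concurrently with hydrotherapy would result in the greater and longer-lasting improvement in motor function".

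**The concern.** The 4- and 12-week evaluations exist to show whether a benefit lasts once treatment stops. Carrying a score forward answers that question by assumption for every child who has left. What is assumed depends on when the child left:

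- **Lost after the 1-week evaluation:** the 1-week score stands in at 4 and 12 weeks, so any gain is treated as fully kept. A child lost after the 4-week evaluation is likewise held at the 4-week score.
- **Lost during treatment:** the only earlier score is baseline, so the child is treated as unchanged at every later visit. These are children aged 4 to 14 (section 2.2), in whom some natural development may occur in either arm.

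The filled-in scores enter the analysis as if they had been measured. The durability conclusion in section 4 can therefore be wrong in either direction, and the result would not show which.

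**Working it through.** **Inputs from the article:** evaluations at baseline and at 1, 4 and 12 weeks after treatment (section 2.5); 150 children, 75 per arm expected (sections 2.1 and 2.3); significance at P < .05 (section 2.8). The article gives no effect size, SD, power or drop-out rate, so the sample size of 150 cannot be reproduced. The point does not depend on it.

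**Assumed:** all effects, drop-out shares, natural gains and correlations below. Drop-out is taken as unrelated to a child's own outcome.

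**Formula.** Let D1 and D12 be the true between-arm effects at 1 and 12 weeks, g1 and g12 the natural gains in both arms, e the share lost before the 1-week visit and l the share lost after it with the 1-week score carried forward. The expected change from baseline at 12 weeks, after filling in, is:

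- treatment: (1 − e − l) × (g12 + D12) + l × (g1 + D1) + e × 0
- control: (1 − e − l) × g12 + l × g1 + e × 0

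With equal drop-out the natural gains cancel. The estimated effect is (1 − e − l) × D12 + l × D1, so

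bias = l × (D1 − D12) − e × D12.

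For children lost only after the 4-week visit, the 4-week effect replaces D1 in the first term.

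**Examples in points, 20% lost late in both arms (e = 0):**

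- D1 = 5, D12 = 1: 0.8 × 1 + 0.2 × 5 = 1.8, against a true 1.0.
- D1 = 5, D12 = 0: 0.8 × 0 + 0.2 × 5 = 1.0, against a true 0.

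**Examples in SD units, equal drop-out, D1 = 0.5:**

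| D12 | e | l | Bias at 12 weeks |
|---|---|---|---|
| 0 | 0 | 20% | 0.2 × 0.5 = +0.10 |
| 0.25 | 0 | 20% | 0.2 × 0.25 = +0.05 |
| 0.25 | 10% | 10% | 0.025 − 0.025 = 0 |
| 0.5 | 0 | 20% | 0 |
| 0.5 | 20% | 0 | −0.2 × 0.5 = −0.10 |

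**Unequal drop-out:**

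- First post-treatment visit, natural gain 3, true effect 3, with 20% of the treatment arm and 10% of control lost before it: 0.8 × (3 + 3) − 0.9 × 3 = 4.8 − 2.7 = 2.1, against a true 3.0.
- 12 weeks, no true effect, natural gain 0.2 SD at 1 week and 0.4 SD at 12 weeks, 5% lost late in treatment, and 20% early plus 10% late in control: (0.95 × 0.4 + 0.05 × 0.2) − (0.70 × 0.4 + 0.10 × 0.2) = 0.39 − 0.30 = +0.09 SD.

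**Effect on the test.** A simulation used 75 per arm, a two-sided t test at 0.05, correlation 0.8 between the 1- and 12-week changes, and 20,000 runs:

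- D1 = 0.5 SD, fully faded by 12 weeks: rejection is 5.0% with no loss, and 6.1%, 9.0% and 14.1% with 10%, 20% and 30% lost late in each arm.
- A lasting effect of 0.5 SD with 20% lost early in each arm: power falls from 86% to 77%.
- The unequal 12-week case above: rejection is 8.6% with no true effect.

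**The case against.** Several objections are fair, and they limit the point.

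- **Direction.** A reader might infer that carry-forward always flatters the treatment. It does not. Children lost during treatment are scored at baseline, which pulls a real effect towards zero.
- **Uneven burden.** Section 2.7.2 plans tDCS on three days and hydrotherapy on two others each week, so a reader might expect heavier drop-out in the treatment arm to inflate the 12-week result. That burden exists only during the 10 weeks, when loss carries the baseline score forward. After treatment both arms have the same evaluations. Section 2.1 also gives all participants 30 sessions, so the control arm's visit load is unclear.
- **Standard error.** A reader might add that filled-in values make the standard error too small. For the between-arm comparison at a single visit this does not hold in general, because each child still supplies one independent value. A simulation with 75 per arm, correlation 0.8 and 20% late loss gave an empirical and a model standard error of 0.163 each, and 4.9% rejection with no effect. The defect at a single visit is bias.
- **Intention to treat as optional.** The opening condition of the rule could be read as letting the analysis set be chosen later. In a sentence about substituting missing data, it most naturally means when data are missing. The wording is loose, but the article does not make the analysis set optional.
- **Severity of the examples.** Near-complete fading with 20% late loss is a severe case, and nothing in the article supports those values. The 1-week comparison is untouched by late carry-forward.
- **Unseen analysis plan.** The lack of a sensitivity analysis in the article is no defect, since a fuller plan may contain one. The carry-forward rule, however, is stated, so it can be judged as it stands.

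What remains is that the one stated rule presumes persistence for late losses and no change for early ones.

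**Conclusion.** The point holds in this limited form. The rule in section 2.8 can bias the 12-week between-arm effect, and so the durability conclusion, by l × (D1 − D12) − e × D12 under equal drop-out. Unequal drop-out combined with natural development adds further bias. The sign is positive when late loss and fading dominate, negative when early loss dominates, and zero when the effect does not fade and all loss is late and equal.

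The structure of the bias follows from the stated rule and visit schedule. Its size does not, because the article gives no drop-out rate, SD, effect or rate of fading. Over the assumed cases with equal drop-out tabulated above, it runs from −0.10 to +0.10 SD. At 30% late loss with a 0.5 SD effect fully faded, it reaches 0.3 × 0.5 = +0.15 SD. These figures are illustrations, not forecasts for this trial.

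**What to change.** In section 2.8, delete the carry-forward rule and its opening condition, and state instead:

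- All randomised children are analysed in the group to which they were assigned.
- GMFM-88 and PBS scores are analysed with a likelihood-based mixed model for repeated measures containing group, visit, group-by-visit interaction and baseline score. Missing scores are assumed missing at random and are not filled in. This model replaces the 2-way ANOVA on filled-in data.
- One sensitivity analysis examines departures from that assumption, for example reference-based multiple imputation. It also covers children with no score after baseline, who contribute no outcome information to a model with baseline as a covariate.

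**Cost:** the article contains no mixed model at present, so this changes the analysis method as well as the wording, and adds one sensitivity analysis. No new data, visits or children are needed.
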